## Abstract

**Background:**

Colorectal cancer (CRC) is one of the most commonly occurring neoplasms and a leading cause of cancer death worldwide, and new preventive strategies are needed to lower the burden of this disease. Eicosapentaenoic acid (EPA), the omega-3 polyunsaturated fatty acid that is widely used in the treatment of hyperlipidemia and prevention of cardiovascular disease, has recently been suggested to have a suppressive effect on tumorigenesis and cancer cell growth. In CRC chemoprevention trials, in general, the incidence of polyps or of the cancer itself is set as the study endpoint. Although the incidence rate of CRC would be the most reliable endpoint, use of this endpoint would be unsuitable for chemoprevention trials, because of the relatively low occurrence rate of CRC in the general population and the long-term observation period that it would necessitate. Moreover, there is an ethical problem in conducting long-term trials to determine whether a test drug might be effective or harmful. Aberrant crypt foci (ACF), defined as lesions containing crypts that are larger in diameter and stain more darkly with methylene blue than normal crypts, are considered as a reliable surrogate biomarker of CRC. Thus, we devised a prospective randomized controlled trial as a preliminary study prior to a CRC chemoprevention trial to evaluate the chemopreventive effect of EPA against colorectal ACF formation and the safety of this drug, in patients scheduled for polypectomy.

**Methods:**

This study is a multicenter, double-blind, placebo-controlled, randomized controlled trial to be conducted in patients with both colorectal ACF and colorectal polyps scheduled for polypectomy. Eligible patients shall be recruited for the study and the number of ACF in the rectum counted at the baseline colonoscopy. Then, the participants shall be allocated randomly to either one of two groups, the EPA group and the placebo group. Patients in the EPA group shall receive oral 900-mg EPA capsules thrice daily (total daily dose, 2.7 g per day), and those in the placebo group shall receive oral placebo capsules thrice daily. After one month’s treatment with EPA/placebo, colonoscopic examination and polypectomy will be performed to evaluate the formation of ACF, and the cell-proliferative activity and cell-apoptotic activity in normal colorectal mucosa and colorectal polyps.

**Discussion:**

This is the first study proposed to explore the effect of EPA against colorectal ACF formation in humans.

This trial has been registered in the University hospital Medical Information Network (UMIN) Clinical Trials Registry as UMIN000008172.

## Background

Colorectal cancer (CRC) is amongst the most commonly encountered neoplasms worldwide [1], and both its prevalence and mortality have been increasing [2]. Removal of colorectal polyps has been to shown to reduce the risk of future development of colorectal cancer and advanced adenoma [3,4] and to thereby prevent colorectal cancer death [5]. On the other hand, patients with polyps (adenomas and/or hyperplastic polyps) also constitute a high-risk group for the development of metachronous colorectal polyps and/or CRC [6]. Therefore, a paradigm shift from surveillance for early detection of cancer or adenomas and polypectomy to new strategies for prevention, including chemoprevention, is needed to lower the burden of this disease. Several large epidemiologic and/or clinical studies have evaluated the possible effects of more than 200 agents, including fiber, calcium, and non-steroidal anti-inflammatory drugs (NSAIDs), including aspirin and selective cyclooxygenase-2 (COX-2) inhibitors, in protecting against CRC development [7]. Our group previously reported that sulindac, a NSAID, had the effect of suppressing the development of sporadic colorectal adenoma [8]. Until date, NSAIDs, especially COX-2 inhibitors, administered either alone or in combination with other agents, have shown the most promise for CRC risk reduction [4], although reports have revealed an increased risk of serious cardiovascular events associated with the use of COX-2 inhibitors [9,10]. In light of the adverse cardiovascular effects of COX-2 inhibitors and the lack of demonstrable efficacy of the other agents that had initially shown promise in this setting, novel drugs that would be both safe and effective for CRC prevention need to be developed. CRC is known to be associated with lifestyle-related diseases, such as hyperlipidemia, diabetes mellitus and obesity [11-14], therefore, we considered that these conditions might represent potential new targets for CRC chemoprevention.

Eicosapentaenoic acid (EPA) is an omega-3 polyunsaturated fatty acid (PUFA) that has long been used widely for primary and also secondary prevention of cardiovascular diseases [15]. EPA impacts the biological functions of adipocytes via two distinct mechanisms; the first, via transcriptional activation of lipogenic and adipogenic genes by binding to nuclear receptors such as Peroxisome Proliferator Activator Receptors (PPARs),[16] and the second, via direct competition with arachidonic acid (AA) incorporation into membrane phospholipids and subsequent conversion to eicosanoids, including prostaglandins (PGs). [17] Recent reports have indicated a lower incidence of colon, breast and prostate cancers in many human populations, associated with a high dietary consumption of omega-3 PUFAs. Multiple reports using a variety of rodent models of early-stage colorectal carcinogenesis, including azoxymethane- and dimethylhydrazine-induced colorectal tumorigenesis (using aberrant crypt foci (ACF) or colonic tumors as the primary endpoint), as well as the Apc^Min/+^ mouse model of familial adenomatous polyposis (FAP), have demonstrated the efficacy of the free fatty acid (FFA) form of a combination of EPA plus docosahexaenoic acid (DHA) (as fish oil substituted for the base fat source in chow).[18] In humans, a phase-III randomized placebo-controlled trial of EPA-FFA 2 g daily for 6 months was performed in 55 patients with FAP undergoing sigmoidoscopic surveillance of a rectal stump after total colrectomy. [19] Patients in the EPA-FFA arm had a significantly lower (by 22.4%) number of lower rectal polyps and a 29.8% decrease in the sum of the polyp diameters in the tattooed area of the rectum as compared with the placebo group. Importantly, daily administration of EPA-FFA 2 g was safe and well-tolerated. [19] NSAIDs chemoprevention trial set in past, first conducted to FAP patients, then applied to sporadic colorectal adenoma/cancer. Thus, much evidence suggests that EPA might be a candidate agent for CRC chemoprevention. In CRC chemoprevention trials, in general, the incidence of polyps or of the cancer itself is set as the study endpoint. Although the incidence rate of CRC would be the most reliable endpoint, use of this endpoint would be unsuitable for chemoprevention trials, because of the relatively low occurrence rate of CRC in the general population [20] and the long-term observation period that it would necessitate. Moreover, there is an ethical problem in conducting a long-term trial to determine whether a test drug may be effective or harmful.

Aberrant crypt foci (ACF), defined as lesions containing crypts that are larger in diameter and stain more darkly with methylene blue than normal crypts,[21-24] are considered as a reliable surrogate biomarker of CRC.[25] We previously reported the usefulness of ACF as a biological marker of CRC, [26,27] and carried out a chemoprevention trial for colorectal ACF. [28,29] Chemoprevention trials with colorectal ACF set as the primary endpoint may have some advantages. First, a long-term observation period is not needed to evaluate the drug effect. Our group reported the n.[29] Long-term trials need much effort and may expose the study participants to an increased risk of development of carcinoma. Second, ACF can be estimated quantitatively. Thus, we devised a prospective randomized controlled trial to evaluate the chemopreventive effect of EPA against the formation of colorectal ACF as a preliminary study prior to CRC chemoprevention trials.

This is the first clinical trial of EPA as a chemopreventive agent against colorectal ACF in humans.

## Methods/design

### Study design and setting

This study is designed as a multicenter, double-blind, placebo-controlled, randomized controlled trial to be performed in patients with colorectal ACF. It will be conducted at the Division of Gastroenterology, Yokohama City University Hospital, and its affiliate hospital, Chigasaki Municipal Hospital and Yokohama Rosai Hospital. The coordinating office shall be at the Yokohama City University Hospital, and the registration, randomized allocation and data collection shall be conducted at this site.

### Ethical considerations and registration

The study protocol is in compliance with the Declaration of Helsinki [30] and the Ethics Guidelines for Clinical Research published by the Ministry of Health, Labour, and Welfare, Japan [31]. We obtained approval for this study from the Ethics committee of Yokohama City University Hospital on May 10, 2012. The protocol and informed consent forms were approved by the institutional ethics committee at each of the participating institutions. This trial has been registered in the University hospital Medical Information Network (UMIN) Clinical Trials Registry as UMIN000008172. Written informed consent for participation in the study will be obtained from all the participating patients. The trial results will be reported in conformity with the Consolidated Standards of Reporting Trials (CONSORT) 2010 guidelines [32].

### Eligibility criteria

Patients with both colorectal ACF and resectable polyps will be recruited for the study.

The proposed inclusion criteria are as follows:

1) Age 40 to 80 years as on the date of informed consent.

2) Willingness to provide written informed consent.

The proposed exclusion criteria are as follows:

1) History of regular use of omega-3 PUFA supplements.

2) History of regular use (defined as at least once per week) of NSAIDs and/or aspirin.

3) History of heart failure, renal failure, liver cirrhosis or chronic hepatic failure.

4) History of familial adenomatous polyposis.

5) History of hereditary non-polyposis colorectal cancer.

6) History of inflammatory bowel disease.

7) Pregnancy or possibility of pregnancy.

8) Patients judged as being inappropriate candidates for the trial by the investigators.

### Intervention

All eligible patients will be allocated randomly to one of two groups, the EPA group and the placebo group. The endoscopists, doctors at the follow-up outpatient clinics, and patients will be blinded to the allocation. Patients in the EPA group shall receive oral 900-mg EPA capsules thrice daily (total daily dose, 2.7 g), and those in the placebo group shall receive oral placebo capsules thrice a day. At the end of 1 month of administration of EPA/placebo, polypectomy will be performed, and the changes in the number of ACF and in the mucosa will be evaluated.

### Outcome measurements

The primary endpoint shall be the change in the number of colorectal ACF after 1-months’s intervention. The endoscopic examinations and polypectomies will be performed using Olympus colonoscopes (model H260AZI). Bowel preparation prior to the colonoscopic procedures will be as described [33,34]. At the time of the first colonoscopy, the endoscope shall be inserted into the cecum, and the entire colorectum will be carefully observed as the endoscope is pulled back. If any polyps are detected, biopsy will be performed. Furthermore, colonic epithelial samples will be obtained. The number of rectal ACF will be counted with a magnifying endoscope, as described [25,33]. At the end of 1 month of administration of EPA/placebo, the same endoscopists will perform the polypectomy and counting of the ACF. All procedures will be recorded on DVD, and all the ACF will be photographed. The number of ACF in each patient will first be counted by the operators during the performance of the colonoscopy. To further ensure validity, the number of ACF will be counted again through observation of the recorded DVD by 3 blinded expert endoscopists ([name], [name], and [name]). If these expert endoscopists judge the colonoscopic examination as having been inadequate in any case, that case will be excluded.

The secondary outcomes shall be (1) the drug safety; adverse events (AEs) will be graded according to the National Cancer Institute Common Toxicity Criteria for Adverse Events (NCI-CTCAE), version 4.0. All study participants shall be provided with a study diary in order to record the daily dosage of the study treatment and the AEs. Patients developing grade 3 or more severe adverse events will be withdrawn from the study at that point; (2) Mucosal fatty acid analysis: Homogenization, extraction and derivatization of the rectal mucosa and polyp fatty acids (EPA, DHA, docosapentaenoic acid (DPA), AA, linolenic acid, linoleic acid, palmitic acid, stearic acid, etc.) shall be performed as described [35]. Fatty acid content shall be determined by gas chromatography–mass spectrometry and expressed as the percentage of the total fatty acid content [36,37]. (3) Effects of EPA on the cell-proliferative and apoptotic activities in the rectal epithelium and polyps: Colonic epithelial samples will be obtained from the same trial patients by biopsy at the time of the first colonoscopy and polypectomy. The cell-proliferative activity will be evaluated by staining for the proliferative cell nuclear antigen (PCNA) and estimation of the Ki-67 labeling indices, and the cell-apoptotic activity by the terminal deoxynucleotidyl transferase-mediated dUTP-biotin nick-end labeling (TUNEL) method. (4) Laboratory data (HDL cholesterol, LDL cholesterol, triglycerides, fatty acid fractions, fasting blood glucose, fasting blood insulin, HbA1c, blood urea nitrogen (BUN), creatinine); (5) physical examination findings (body weight, body mass index (BMI)). EPA is widely used as an anti-hyperlipidemic drug that improves the plasma lipid profile. The effect of EPA on the plasma lipid profile will be evaluated by comparing these parameters measured at the baseline with those measured after 1 month of treatment in the EPA group and placebo group. All participants will undergo a physical examination and laboratory tests at the time of the baseline endoscopic examination and polypectomy.

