### Sample size estimation

In the chemoprevention trial conducted in FAP patients, the NSAID sulindac and selective cyclooxygenase-2 (COX-2) inhibitor celecoxib reduced polyposis of the retained rectum after colectomy with ileorectal anastamosis (IRA). As previously noted, EPA has a suppressive effect for polyp formation and proliferation of FAP [19]. From these reports, we estimated that NSAIDs and EPA may have equivalent effect on suppression of polyp formation and proliferation.

Based on the target in the NSAIDs chemoprevention study for ACF, Takayama et al. reported that sulindac administration at 300 mg/d for 2 months to post-polypectomy patients suppressed ACF formation, decreasing the number of ACF from 7.70 ± 4.04 (baseline) to 4.00 ± 2.95 (at 2 months, *p < 0.001*) [33]. Presuming EPA and sulindac may have equivalent effect in suppressing ACF formation, to detect the reduction in the number of ACFs in the EPA group using the Mann–Whitney U test with a two-sided significance level of 5% and a power of 80%, it was estimated that a sample size of 12 patients per group would be necessary. Assuming a 10% dropout rate, we propose to recruit 15 patients per group, that is, a total of 30 patients.

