This trial may have the following limitations. First, ACF are considered as a reliable surrogate biomarker of CRC, [21] although their biological significance still remains controversial. In CRC chemoprevention trials, in general, the incidence of polyps or of the cancer itself is set as the study endpoint. Although the incidence rate of CRC would be the most reliable endpoint, use of this endpoint would be unsuitable for chemoprevention trials, because of the relatively low occurrence rate of CRC in the general population [18] and the long-term observation period that it would necessitate. We previously reported the usefulness of ACF as a biological marker of CRC [26,27] and carried out a chemoprevention trial for colorectal ACF [28,29]. Thus, we devised a trial using this endpoint (ACF) to evaluate the chemopreventive effect of EPA. Second, we do not propose to conduct a dose–response study in respect of the effect of EPA on ACF formation. Until now, trials of EPA for cancer prevention and adjuvant treatment have been conducted using EPA at doses of 1000 – 4000 mg per day. In Japan, the EPA drug product specification is 0.9 g, and 2.7 g of EPA has been commonly used and very well tolerated. Therefore, we planned to conduct this trial using 2.7 g of EPA per day. Third, an intervention period of 1 month may be too short to allow reliable detection of differences between the groups. However, we showed in a previous study that oral administration of metformin for 1 month suppressed the formation of colorectal ACF in humans [29]. If the intervention agents had a chemopreventive effect, an intervention period of 1 month would be sufficient to evaluate the changes in the number of ACF.

We previously conducted a short-term chemoprevention trial of metformin for colorectal ACF, and showed the suppressive effect of the drug on the formation of ACF. Thereafter, we are conducting a long-term metformin chemoprevention trial for colorectal polyps, the trial registered in the UMIN Clinical Trials Registry as UMIN000006254 [34]. We propose to repeat the same step for the chemoprevention trial using EPA.

If EPA were found to be effective for the prevention of CRC, the impact would be extremely large. We consider it of interest, therefore, to determine whether EPA might suppress the formation of human colorectal ACFs.

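### A grade 3 or worse adverse event removes the patient from the study rather than only from study drug, so the 1-month ACF count is lost and later adverse events are not secured

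*Protocol article*

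**What the plan says.** Under Outcome measurements, within the safety item, the protocol article says that "Patients developing grade 3 or more severe adverse events will be withdrawn from the study at that point". It names the study, not the study drug. It sets no condition on causality and does not distinguish the blinded arms.

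The same section defines the main outcome: "The primary endpoint shall be the change in the number of colorectal ACF", assessed after one month. The follow-up count is tied to a single visit: "At the end of 1 month of administration of EPA/placebo, the same endoscopists will perform the polypectomy and counting of the ACF". The Intervention section gives the same timing: "At the end of 1 month of administration of EPA/placebo, polypectomy will be performed".

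Adverse events are collected by diary: "All study participants shall be provided with a study diary in order to record the daily dosage of the study treatment and the AEs". Safety is the first secondary outcome listed, and the Statistical analysis section compares it between groups by chi-square test.

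On numbers, Sample size estimation says that "a sample size of 12 patients per group would be necessary", and raises this to 15 per group for an assumed 10% dropout. The article gives no expected rate of grade 3 or worse events. The nearest statement, in the Discussion, is that "2.7 g of EPA has been commonly used and very well tolerated".

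**The concern.** Stopping study drug after a severe event is sound clinical care. Removing the patient from the study is a separate decision, and it costs data. The event occurs after randomisation, and treatment may affect how often it occurs and in whom. Leaving out the patients who have it means that the groups compared are no longer quite the groups randomised. Blinding does not prevent this, because the selection comes through the event itself. Recruiting extra patients for dropout restores numbers, not comparability.

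Two things are at stake: possible selection bias in the primary ACF comparison, and incomplete later safety data in the patients with the most severe toxicity. Follow-up tissue, laboratory and physical measurements are also taken at the 1-month visit, so they would go missing as well.

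**Working it through.** **Reading the text.** The rule removes the patient when the event occurs. The only follow-up ACF count comes at one month. Nothing in the article provides for an ACF count or adverse event recording after withdrawal. The statement that all participants have examinations and laboratory tests at baseline and polypectomy is a general schedule and does not exempt withdrawn patients. An event before the 1-month visit therefore leaves no primary outcome. The triggering event itself is still graded and counted.

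**The plan's own allowance.** 12/(1 − 0.10) = 13.3, rounded up to 14 per group. The plan recruits 15, so up to three losses per group from all causes still leave 12.

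**How often.** Inputs: 30 patients, 15 per arm (Sample size estimation). The event rate r is assumed, independent between patients and equal in both arms.

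- Expected losses = 30r
- Chance of at least one loss in the trial = 1 − (1 − r)^30
- Chance of three or more, or four or more, losses in a given arm: binomial with n = 15

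| r | Expected losses | At least one of 30 | Three or more in a given arm | Four or more in a given arm |
|---|---|---|---|---|
| 1% | 0.3 | 26.0% | 0.04% | 0.001% |
| 2% | 0.6 | 45.5% | 0.3% | 0.02% |
| 5% | 1.5 | 78.5% | 3.6% | 0.5% |
| 10% | 3.0 | 95.8% | 18% | 5.6% |

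**Bias.** Inputs: means 7.70 and 4.00 (difference 3.70) and SDs 4.04 and 2.95, from the sulindac study cited in Sample size estimation. If k patients, each lying d from the arm mean in the same direction, drop out of 15, the mean of the rest shifts by k·d/(15 − k). Taking d as one SD:

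- k = 1: 2.95/14 = 0.21 to 4.04/14 = 0.29 ACF, which is 6–8% of 3.70.
- k = 3: 3 × 2.95/12 = 0.74 to 3 × 4.04/12 = 1.01 ACF, which is 20–27% of 3.70.

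These figures illustrate scale only. They use SDs of raw counts because the SD of change is not given, and they describe means although the planned test is rank-based.

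**Power.** Simulated Mann–Whitney test, two-sided 5%, 20,000 runs, with the means and SDs above and placebo assumed to stay at baseline:

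| Evaluable patients | Normal data | Negative binomial counts |
|---|---|---|
| 15 v 15 | 75.2% | 80.0% |
| One lost from one arm | 73.3–74.1% | 77.6–78.1% |
| Three lost from one arm | 70.2–70.6% | 74.5–74.6% |

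One loss costs about 1–2 points. Whether 12 per group gives 80% power at all is a separate matter and does not affect this point.

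**The case against.** The strongest reply is that the harm needs two steps, the stated rule and no data collection afterwards, and only the first is in the text. A journal article may leave follow-up after withdrawal to the full protocol. These patients were already scheduled for polypectomy, so the colonoscopy may happen anyway. That stands as a limit: the full protocol may continue follow-up. But the article states a specific rule, and nothing in it makes a count taken at such a polypectomy trial data.

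The second reply is size. Treatment lasts one month. The Discussion calls the dose very well tolerated, the Background reports 2 g daily for six months as safe, and the Eligibility criteria exclude heart failure, renal failure, cirrhosis and chronic hepatic failure. At 1–2%, no loss at all is the likelier result (0.99^30 = 74%; 0.98^30 = 55%). Multiplying the expected 0.15–0.30 losses per arm by the 0.21–0.29 shift gives 0.03–0.09 ACF, about 1–2% of 3.70. Three losses in one arm, all deviating the same way, is unlikely, and no mechanism linking severe events to ACF count is known from the article. All of this stands and keeps the point modest.

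Third, if safety is compared by patient, a withdrawn patient already counts as having had a grade 3+ event, and only further events within the rest of the month are lost. That also stands, as a limit on the safety harm.

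Finally, counting off-drug patients is partly a choice of estimand, and some patients will be unfit for colonoscopy. Both are true, but neither is a reason to discard the counts that can be obtained.

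**Conclusion.** The point holds. As written, the rule forfeits the primary outcome of a randomised patient because of a post-randomisation event that treatment may affect, and no other part of the article offsets it. It probably affects zero or one patient. For one patient a plausible shift is 6–8% of the assumed difference in either direction, with little loss of power. The 5–10% event rates and the three-loss case are outer bounds, not expectations.

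The conclusion about the wording rests on no assumed number. The size rests on the assumed event rates, a one-SD deviation and the SDs borrowed from the sulindac study. The rule should be changed because the risk is avoidable at almost no cost.

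**What to change.** Replace the sentence with, for example: *If a grade 3 or worse adverse event occurs, study drug is stopped. The patient stays in follow-up, and adverse events are recorded to the planned end. The ACF count is taken at the planned polypectomy if this is clinically safe and takes place. The patient is analysed in the group randomised.* Withdrawal of consent still ends follow-up. An on-treatment analysis can be added as a supplement.

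The decision to stop drug is unchanged, and no procedure is added when the planned polypectomy goes ahead. The cost is some counts made off drug: one EPA patient in 15 with no effect at all would lower the assumed difference from 3.70 to 3.70 × 14/15 = 3.45. Some patients will decline the 1-month colonoscopy or be unfit for it, so the change recovers most but not necessarily all of the missing counts. If the full protocol already continues follow-up, correct the article's wording to match.

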### Statistical analysis

The number of ACFs in each group, the primary endpoint, will be compared between the EPA group and the placebo group by the Mann–Whitney U test. The safety, one of the secondary endpoints, will be compared by the chi-square test. The remaining results in the two groups will be compared by the Mann–Whitney U test or Student’s *t* test. A P values of < 0.05 will be regarded as indicative of significance. The analysis will be performed using SPSS, version 17.0 (SPSS Inc., Chicago, Il.).

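### The sentence on how EPA's effect on plasma lipids will be judged describes a before-after comparison in each group, and is not reconciled with the two-group tests in the analysis section.

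*Protocol article*

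**What the plan says.** Lipids are part of the fourth secondary outcome in the protocol article, Outcome measurements: "Laboratory data (HDL cholesterol, LDL cholesterol, triglycerides, fatty acid fractions" and further laboratory values. The same section then says how they will be used: "The effect of EPA on the plasma lipid profile will be evaluated", with the method given as "evaluated by comparing these parameters measured at the baseline with those measured after 1 month of treatment in the EPA group and placebo group". Laboratory tests are scheduled twice, at the baseline endoscopy and at polypectomy.

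The Statistical analysis section does not mention lipids by name. They fall under its general rule: "The remaining results in the two groups will be compared by the Mann–Whitney U test or Student’s" t test. The threshold is stated once for all outcomes: "A P values of < 0.05 will be regarded as indicative of significance". No paired test is named anywhere. The section does not say whether the quantity compared is the 1-month value or the change from baseline.

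**The concern.** The sentence in Outcome measurements claims to evaluate an effect of EPA, so it reads as inference and not as description. Yet the two things it compares are baseline and 1-month values; the groups appear only as the places where the comparison is made. A before-after change contains whatever else moved over the month, such as diet or time, along with any drug effect. Only the contrast between randomised groups removes what they share. A stable placebo group cannot be presumed either, because the placebo is itself a fat (medium-chain triglycerides; Drug supply section).

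An analyst who follows Outcome measurements literally has no suitable test, since the named tests are unpaired. An analyst who follows Statistical analysis is not making the comparison that Outcome measurements describes. At stake is a secondary claim that EPA improved lipids when the two groups did not differ.

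**Working it through.** **No figure to reproduce.** The protocol gives no effect size, standard deviation or power for any lipid. Its sample size calculation concerns the ACF count only.

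**The two sections side by side.**

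| | Outcome measurements | Statistical analysis |
|---|---|---|
| What is compared | Baseline with 1 month | EPA with placebo |
| Role of placebo group | A second place where the comparison is made | The comparator |
| Test named | None | Mann–Whitney U or Student's t (unpaired) |
| Quantity tested | Not a between-group contrast | Not stated (1-month value or change) |

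**Inputs for the error-rate check.**
- Patients per group: 12 evaluable, 15 recruited (Sample size estimation).
- Significance level: 0.05 (Statistical analysis), taken as two-sided. The protocol says two-sided only for the primary endpoint.
- Assumption, not in the protocol: both groups have the same true mean change, d standard deviations of the change, with d from 0 to 1. There is then no treatment effect.

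**Formulas.** Let w be the probability that a within-group test of the change is significant. The groups are independent, so with equal true change:
- P(EPA significant, placebo not) = w(1 − w), at most 0.5 × 0.5 = 0.25.
- P(exactly one group significant) = 2w(1 − w), at most 0.50.

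**Results.** Simulation with 100,000 replicates per setting and normally distributed changes. The within-group test is a one-sample t test on the change; the between-group test is a two-sample t test on the change. Each cell gives n = 12 / n = 15.

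| d | EPA group significant (w) | EPA significant, placebo not | Between-group test significant |
|---|---|---|---|
| 0 | 0.050 / 0.050 | 0.047 / 0.048 | 0.050 / 0.050 |
| 0.25 | 0.124 / 0.145 | 0.109 / 0.124 | 0.051 / 0.049 |
| 0.5 | 0.352 / 0.437 | 0.226 / 0.245 | 0.049 / 0.050 |
| 0.57 | 0.437 / 0.540 | 0.245 / 0.248 | 0.050 / 0.049 |
| 0.75 | 0.659 / 0.772 | 0.225 / 0.177 | 0.050 / 0.049 |
| 1.0 | 0.884 / 0.948 | 0.102 / 0.049 | 0.049 / 0.051 |

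The simulation agrees with the formula: at n = 12 and d = 0.5, 0.352 × 0.648 = 0.228 against 0.226 simulated.

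The split pattern therefore ranges from about 5% to about 25% over the assumed shifts. It is low at both ends: with no shared shift few tests are significant, and with a large one both groups usually are. These figures ignore direction; at d = 0 only about half of the 5% would favour EPA. The between-group test holds 5% throughout.

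**The case against.** The strongest reply is that a between-group test is already specified. Lipids are among the remaining results, and the analysis section compares those between the groups. The outcomes sentence would then only say which measurements are used and that they come from both groups. It names no paired test, no per-group P value and no rule for declaring an effect from one group's result. That only unpaired tests are planned suggests that no within-group inference is intended.

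Much of this stands. A reader might infer that the protocol contradicts itself, or that it has settled on judging lipids by per-group significance. The text supports neither: the harmonised reading is available, and the figures above describe a decision rule that the protocol never states. A reader might also take 25% as the false-positive rate of the plan. It is the peak of a range that depends on an assumed shift.

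Two sources of bias that come to mind are weakly supported. Laboratory tests accompany a colonoscopy at both visits, so bowel preparation is not an evident cause of a before-after shift. There is no lipid entry criterion, so systematic regression to the mean is not expected.

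The wording is also confined to plasma lipids. Mucosal fatty acids, proliferation and apoptosis indices, glucose and weight carry no such sentence and fall under the two-group tests.

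What the reply does not remove is that the harmonised reading has to be supplied by the reader. The only sentence on how the lipid effect is judged names a comparison that does not use the placebo group as a control. A full protocol or analysis plan that is not shown may settle the details, but this sentence would still need rewording.

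**Conclusion.** The point holds as a minor defect of wording with a methodological consequence. Taken literally, the outcomes sentence is not a test of treatment and does not match the two-group tests in the analysis section; the document leaves the two unreconciled.

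If per-group tests were used for inference, the misleading split pattern would occur in about 5% to 25% of trials with no treatment effect, for a shared shift of 0 to 1 standard deviation of the change. The size of that shift, the normality of the changes and the use of t tests are assumptions. That a within-group test does not control the error rate for a treatment effect once the groups share a shift does not depend on its exact size.

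Lipids are an unpowered secondary outcome. The sample size and the primary endpoint are not affected.

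**What to change.** In Outcome measurements, replace the sentence on the lipid profile with:

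*The effect of EPA on each plasma lipid is the difference between the EPA and placebo groups at 1 month, adjusted for the baseline value (ANCOVA, log scale for triglycerides), with 95% CI; within-group changes are descriptive only, without P values.*

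Add the same analysis to Statistical analysis, which at present offers only Mann–Whitney U or Student's t for these results. ANCOVA is not needed for validity, since a between-group test on the change also holds 5%. It is preferred because it uses the baseline value already collected and allows for chance imbalance: baseline lipids are not among the minimisation factors (age, gender, BMI, institution), and there are only 15 patients per group.

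The same baseline-adjusted comparison may be used for other continuous secondary outcomes measured at both visits. That would be an improvement, not the correction of an error in the text.

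The cost is a wording change, best dated before unblinding. It needs no new visits, measurements or patients.
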